| **Session** | **Content** |
| --- | --- |
| 1 | - Introduction to body image - Personal reflection upon the impact of body image concerns - Exploration of personal goals |
| 2 | - Introduction to the CBT approach - Physiological symptoms of anxiety - Exploration of body image and self-esteem - Relaxation training |
| 3 | - Stopping negative body-related self-talk - Developing alternative, balanced thoughts - Planning a self-care activity schedule - Relationship between body function and movement |
| 4 | - Sociocultural pressures for women in midlife - Internalisation of the youthful-thin ideal - Body comparisons – experimental activity - Body nurture with accepting self-talk |
| 5 | - Exploration of relationships and intimacy - Managing people’s reactions - Cognitive restructuring process - Physical activity and movement |
| 6 | - Identifying core beliefs - Modifying mistaken beliefs - Engaging the senses – mindful eating - Relaxation exercise |
| 7 | - Positive body affirmations - Reducing the chances of a setback - Dealing with a setback - Future plans |

- 1. **Intervention facilitators and fidelity**

Based on 60 women being in the intervention arm, and approximately 8 women per group, there will be approximately 6-8 ABC groups, running in both parallel and sequentially. Each group will be delivered jointly by two Cancer Support Specialist (CSS) (e.g. a Psychologist a nurse) from a Maggie’s centre. However, there will be a different pair of facilitators across each group, with some running only one group and others running up to three (depending on the capacity).

Working for a cancer support service, facilitators already have knowledge and skills to support people treated for breast cancer. Their expertise also complements one another, as the psychologist has undergone psychotherapeutic training (and thus can confidently deliver the CBT elements), whilst the CSS understands the treatment experience and impacts (e.g., on body functionality, intimacy), and thus can deliver the other intervention elements. All facilitators will receive two days of online training from the PI, who has considerable experience in training facilitators to deliver body image interventions (including ABC). They will be provided with materials and encouraged to make notes during the training to help support them during deliver of the ABC sessions.

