The self-report outcome measures (K10, BAS-2, FACT-B: Breast Cancer Subscale, Hopwood Body Image Scale, and BREAST-Q: Sexual Well-Being Scale) are each well-established validated measures which will be scored according to the most appropriate guidelines. The design (pre- post- two arm parallel randomised controlled trial) and the selected measures are amenable to analysis using long-established statistical techniques. The analysis will proceed using the intention-to-treat analysis set with the statistician blinded to allocation. These analyses include:

- Descriptive statistics (including mean and standard deviation) by randomised arm at each time point (T1, T2, T3, and T4).
- Unadjusted statistical comparison between arms at each timepoint (T1, T2, T3, and T4) using the independent samples *t*-test with 95% and 80% confidence intervals and quantification of effect size using Cohen’s *d*. If statistical assumptions do not seem tenable, robust non-parametric bootstrap equivalent tests will be used.
- Adjusted statistical comparison between arms at each timepoint (T2, T3, T4) will be conducted controlling for commensurate baseline measures using ANCOVA (Analysis of Covariance) along with 95% and 80% covariate adjusted confidence intervals and quantification of effect size using partial eta -squared. If statistical assumptions do not seem tenable, robust remedies will be considered, including a baseline by randomised arm interaction effect, or homoscedasticity corrected robust standard errors (HC3) or the robust non-parametric bootstrap equivalent ANCOVA.
  1. **Heath economic evaluation**

The draft ABC AD-SUS (Appendices 23-25) will undergo testing for the following:

- Acceptability: This will be assessed via the proportion of participants completing the measure, percentage of missing items, and consideration of the clarity of any questions associated with missing data.
- Comprehensiveness: This will be assessed via open-ended questions included in the AD-SUS asking participants to report any ‘other’ services not reported elsewhere in the measure (missing items).
- Redundancy: This will be assessed through consideration of any service items included in the AD-SUS but not reported as being used by any participant (redundant items).

These results, plus feedback from participants, will inform a final version of the AD-SUS for a future definitive trial.

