**12.24 Appendix 24: Modified version of the Adult Service Use Schedule: T3**

**Accepting your Body after Cancer (ABC)**

**USE OF HEALTH AND SOCIAL CARE SERVICES**

**INSTRUCTIONS**

It would be helpful for us to know what types of health and social care services you have used since you entered the ABC study approximately 5 months ago. These can be services that you received in a hospital or in the community (for example, in a GP surgery, a community health centre or in your home).

If you are in the ABC therapy group, please **EXCLUDE YOUR USE OF THE ABC THERAPY**, as it is important that ABC research staff are unaware of who is receiving the ABC therapy.

Some of the services listed in this questionnaire may not be relevant to you, but it would still be helpful for us to know this, so **please select ‘No’ if you have not used any of the services listed**.

We understand that you may not remember the exact number of appointments you have had for the services you have used, but **please give us your best guess**.

1. **HOSPITAL SERVICES INVOLVING AN OVERNIGHT STAY**

We would like to know if you have stayed overnight in hospital since you entered the ABC study approximately 5 months ago.

For each reason listed, please tell us if you have stayed overnight in hospital for this reason by selecting ‘Yes’ or ‘No’.

If the answer is ‘Yes’, please tell us how many nights in total you stayed overnight in hospital for this reason since you entered the ABC study approximately 5 months ago.

If you had overnight stays in a hospital on more than one occasion for the same reason, please report the total number of nights for all occasions.

| **Reason** | **Yes** | **No** | **If yes, please enter the total number of nights you stayed in hospital for this reason since you entered the ABC study approximately 5 months ago** |
| --- | --- | --- | --- |
| **Overnight stay in hospital for reasons related to cancer** |  |  |  |
| **Overnight stay in hospital for reasons related to your mental health** |  |  |  |
| **Overnight stay in hospital for any other reason** |  |  |  |

1. **HOSPITAL SERVICES THAT DID NOT INVOLVE AN OVERNIGHT STAY**

We would like to know if you have had any appointments in hospital since you entered the ABC study approximately 5 months ago. These are hospital appointments where you DID NOT stay in hospital overnight and are commonly called outpatient or day-patient appointments.

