**Please include all contacts, whether they took place in person, by telephone or online by video conference.**

|  | **Yes** | **No** | **If yes, please enter the total number of contacts you had since you entered the ABC study approximately 5 months ago** |
| --- | --- | --- | --- |
| **General practitioner (GP)** |  |  |  |
| **Practice nurse (a nurse based in a GP surgery)** |  |  |  |
| **Cancer nurse/breast cancer nurse in the community (please exclude any contacts with a breast cancer nurse in hospital)** |  |  |  |
| **Any other nurse in the community, for example a district nurse, health visitor or midwife** |  |  |  |
| **Cancer support specialist/cancer support worker** |  |  |  |
| **Social worker, family support worker or any other social services worker** |  |  |  |
| **Any therapist providing ‘talking therapy’, for example cognitive behaviour therapy, counselling, mindfulness-based therapy, dialectical behaviour therapy, etc.**  ****If you are in the ABC therapy group, please EXCLUDE your use of the ABC therapy**** |  |  |  |
| **Excluding any contacts with therapists already reported in the previous question, any other mental health worker in the community, for example a psychiatrist, a Community Psychiatric Nurse (CPN), a Community Mental Health Team (CMHT) worker, etc.** |  |  |  |
| **Excluding any contacts already reported in previous questions, any other advice or support relating to cancer (either online, over the phone or in person) from a charitable organisation such as Macmillan Cancer Support, Maggie’s Centres, Penny Brohn, Breast Cancer Now, Keeping Abreast, Flat Friends, Look Good Feel Better, OUTpatients (formerly known as Live Through This), Switchboard Black Women Rising, etc.** |  |  |  |
| **Excluding any contacts already reported in previous questions, any other advice or support relating to mental health (either online, over the phone or in person) from a charitable organisation such as the Samaritans, MIND, Macmillan, etc.** |  |  |  |

1. **MEDICATION**

We would like to know if you have been prescribed any medication by a doctor or other health professional for mental health or cancer-related reasons in the last 5 months. This might include, for example, medication for depression, anxiety, sleep disorders, etc, or hormone blocking medications.

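### The T3 service-use form excludes ABC on its front page, but in the community table repeats this only in the talking-therapy row, although ABC also fits the cancer support specialist row and the charity row naming Maggie's.

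*Protocol*

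**What the plan says.** Section 6.1 describes ABC as seven group sessions held online over seven consecutive weeks. Section 6.2 says who runs them: "Each group will be delivered jointly by two Cancer Support Specialist (CSS) (e.g. a Psychologist a nurse) from a Maggie’s centre".

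Appendix 24 is the modified AD-SUS given at T3. It looks back about five months, to study entry, so its window contains the planned sessions. The opening instructions tell women in the ABC group to "EXCLUDE YOUR USE OF THE ABC THERAPY". The reason given there is that research staff should not learn who is receiving ABC.

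The community-services table in the same appendix starts with a general request: "Please include all contacts, whether they took place in person, by telephone or online by video conference". Its talking-therapy row then carries a reminder: "If you are in the ABC therapy group, please EXCLUDE your use of the ABC therapy". No other row does. Two of the rows without it are:

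- "Cancer support specialist/cancer support worker", which comes before the talking-therapy row;
- the charity row, which comes after it. This row opens "Excluding any contacts already reported in previous questions, any other advice or support relating to cancer" and covers help given "either online, over the phone or in person) from a charitable organisation such as Macmillan Cancer Support, Maggie’s Centres".

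Section 7.3 treats the AD-SUS as a draft to be tested for acceptability, comprehensiveness and redundancy, with service use summarised descriptively. Section 5.5 says the Health Economist is blinded to condition.

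**The concern.** The protocol's authors evidently thought one reminder on the front page might not be enough, because they added a second at a row where ABC could be entered. They chose the row that matches ABC's type of therapy. The rows that match its provider and its setting have no reminder.

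A woman filling in the table meets a request to count everything, including video contacts. She then meets a row bearing the job title of her ABC facilitators. Appendix 9, completed at T2, has already used that title when asking about the people delivering the programme. Later she meets a row for online cancer support that names Maggie's. If she no longer has the front page in mind, or reads the single reminder as applying to its own row only, her ABC sessions can end up in either place.

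The trial treatment would then be recorded as background care, and only in the intervention arm. Adapting and testing this measure is one of the study's primary objectives, and the results are to shape the version used in the definitive trial. A weakness left in the form now could be carried forward.

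**Working it through.** The protocol states no figure on this point, so there is nothing to reproduce. The check sets ABC's features against the ten rows of the T3 community table and then bounds the possible error.

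**Which rows fit ABC**

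| Row | Fit with ABC | Reminder in the row? |
| --- | --- | --- |
| 5, cancer support specialist or worker | Matches the facilitators' job title (section 6.2) | No |
| 7, talking therapy, including CBT | Matches the type of therapy | Yes |
| 9, cancer support from a charity, online included, Maggie's named | Matches provider, setting and mode (sections 6.1 and 6.2) | No |
| 10, mental health support from a charity | Weaker fit; Maggie's not named | No |

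One well-fitting row therefore comes before the reminder and one comes after it.

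**Does the de-duplication wording help?** Row 9 removes only contacts already entered above. A woman who correctly left ABC out of row 7 has not entered it, so this wording does not keep ABC out of row 9. The front-page instruction does that alone. The same wording does stop a session entered in row 5 from being entered again in row 9.

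**Ceiling on the error**

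Inputs: 7 sessions (section 6.1); 60 women in the intervention arm (trial summary); each session entered at most once, from the de-duplication wording.

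- Per woman: 7 contacts.
- Intervention arm: 60 x 7 = 420 contacts.
- Control arm: 0, since controls attend no ABC sessions.

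**Across misreporting rates.** The protocol gives no rate, so the share p of women who attend all sessions and enter them is an assumption. The arm total is 420 x p and the arm mean is 7 x p.

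| Assumed p | Spurious contacts | Added to the arm mean |
| --- | --- | --- |
| 0% | 0 | 0 |
| 10% | 42 | 0.7 |
| 50% | 210 | 3.5 |
| 100% | 420 | 7 |

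Incomplete attendance lowers every figure in proportion.

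**The T4 form.** Appendix 25 has the same layout, but its window of about three months runs from T3 (week 20) to T4 (week 32). T2 is placed at week 9, within a week of the last session. On the planned schedule, no ABC session falls in the T4 window.

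**The case against.** The strongest reply is that the matter is already handled. The exclusion stands in bold capitals on the front page, before any section, and governs every row. A woman who follows the form reports no ABC contacts anywhere. That a single repeat would lead her to think the rule applies only there is a judgement about how people read forms, and nothing in the protocol demonstrates it. This reply stands as far as it goes: the plan contains no contradiction here, and the correct count under its own instructions is zero. It does not explain why a reminder was thought useful in one row and not in two others that fit ABC at least as well.

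Four stronger readings might be inferred, and the protocol does not support them.

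- *Double counting across rows, giving 2 x 420 = 840.* This needs women to ignore the de-duplication wording as well as the front page. The ceiling under that wording is 420.
- *ABC would be costed twice in this study.* Section 7.3 plans a descriptive summary of service use and no cost comparison between arms.
- *The redundancy test would be spoiled.* An item counts as redundant only if it falls among "any service items included in the AD-SUS but not reported as being used by any participant (redundant items". The same rows are asked at T1, before any ABC session, and of controls, and Maggie's is one of the recruitment routes. A mistaken entry matters only if nobody else reports that service at all.
- *Errors could be cleaned later against ABC group dates.* The table records yes or no and a total, with no contact dates, so this check cannot be done from the form.

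It is also fair to say that finding unclear items is part of what this study is for. That argues for mending a visible one.

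**Conclusion.** The point holds as a modest form-design weakness. The exclusion exists and covers the whole form. Its row-level reminder is placed by type of therapy only, and two rows that match ABC's provider and online delivery are left without it. The resulting risk lies wholly in the intervention arm.

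Its size is at most 7 contacts per woman, or 420 in the arm. This assumes that all 60 women attend every session, that all of them overlook the front page, and that each session is entered once. The true number depends on an unknown misreporting rate and may be zero.

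A second consequence follows from the form's own stated purpose. A total of about seven specialist or charity contacts at T3 could suggest allocation to the Health Economist, who is meant to be blinded. This is a possible hint and not proof of unblinding, since a control could also have used such services.

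Nothing here affects the feasibility outcomes or the comparison of the psychological measures. The case for acting is that the change costs almost nothing and that the form is itself under test.

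**What to change.** In Appendix 24, repeat the exclusion at the head of the community-services table, beside the request to count all contacts. A short line would do, for example: *do not count ABC programme sessions*. Alternatively, put the same line in the cancer support specialist row and in the charity row that names Maggie's. The word *programme* is worth using because the participant feedback forms (Appendices 9, 10 and 31) use it for ABC.

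Carry the wording into the final AD-SUS for the definitive trial, where service use is to support cost estimates. The same line in Appendix 25 would be precautionary only, for women whose sessions ran late.

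The cost is one line on a questionnaire, the amendment procedure for a changed participant document, and a slightly longer form. No analysis has to change.

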**12.25 Appendix 25: Modified version of the Adult Service Use Schedule: T4**

**Accepting your Body after Cancer (ABC)**

**USE OF HEALTH AND SOCIAL CARE SERVICES**

**INSTRUCTIONS**

It would be helpful for us to know what types of health and social care services you have used since you last completed the ABC questionnaires approximately 3 months ago. These can be services that you received in a hospital or in the community (for example, in a GP surgery, a community health centre or in your home).

If you are in the ABC therapy group, please **EXCLUDE YOUR USE OF THE ABC THERAPY**, as it is important that ABC research staff are unaware of who is receiving the ABC therapy.

Some of the services listed in this questionnaire may not be relevant to you, but it would still be helpful for us to know this, so **please select ‘No’ if you have not used any of the services listed**.

We understand that you may not remember the exact number of appointments you have had for the services you have used, but **please give us your best guess**.

1. **HOSPITAL SERVICES INVOLVING AN OVERNIGHT STAY**

We would like to know if you have stayed overnight in hospital since you last completed the ABC questionnaires approximately 3 months ago.

For each reason listed, please tell us if you have stayed overnight in hospital for this reason by selecting ‘Yes’ or ‘No’.

If the answer is ‘Yes’, please tell us how many nights in total you stayed overnight in hospital for this reason since you last completed the ABC questionnaires approximately 3 months ago.

If you had overnight stays in a hospital on more than one occasion for the same reason, please report the total number of nights for all occasions.

| **Reason** | **Yes** | **No** | **If yes, please enter the total number of nights you stayed in hospital for this reason since you last completed the ABC questionnaires approximately 3 months ago** |
| --- | --- | --- | --- |
| **Overnight stay in hospital for reasons related to cancer** |  |  |  |
| **Overnight stay in hospital for reasons related to your mental health** |  |  |  |
| **Overnight stay in hospital for any other reason** |  |  |  |

1. **HOSPITAL SERVICES THAT DID NOT INVOLVE AN OVERNIGHT STAY**

We would like to know if you have had any appointments in hospital since you last completed the ABC questionnaires approximately 3 months ago. These are hospital appointments where you DID NOT stay in hospital overnight and are commonly called outpatient or day-patient appointments.

For each reason listed, please tell us if you had any appointments in a hospital for this reason by selecting ‘Yes’ or ‘No’.

If the answer is ‘Yes’, please tell us how many appointments in total you had for each reason since you last completed the ABC questionnaires approximately 3 months ago.

| **Reason** | **Yes** | **No** | **If yes, please enter the total number of hospital appointments you have had for this reason since you last completed the ABC questionnaires approximately 3 months ago** |
| --- | --- | --- | --- |
| **Hospital appointment for reasons related to cancer** |  |  |  |
| **Hospital appointment for reasons related to your mental health** |  |  |  |
| **Hospital appointment for any other reason** |  |  |  |

1. **ACCIDENT AND EMERGENCY SERVICES**

We would like to know if you have been to an Accident and Emergency Department (A&E) since you last completed the ABC questionnaires approximately 3 months ago.

Please tell us if you have been to an A&E by selecting ‘Yes’ or ‘No’.

If the answer is ‘Yes’, please tell us the total number of times you have visited A&E since you last completed the ABC questionnaires approximately 3 months ago.

|  | **Yes** | **No** | **If yes, please enter the total number of times you visited an A&E department since you last completed the ABC questionnaires approximately 3 months ago** |
| --- | --- | --- | --- |
| **Accident and Emergency (A&E) contacts** |  |  |  |

1. **AMBULANCE**

We would like to know if you have received any treatment by an ambulance crew since you last completed the ABC questionnaires approximately 3 months ago. This may include treatment by an ambulance crew in the community and/or travel to hospital in an ambulance.

Please tell us if you have been treated by someone in an ambulance by selecting ‘Yes’ or ‘No’.

If the answer is ‘Yes’, please tell us the total number of times you have been treated by someone in an ambulance since you last completed the ABC questionnaires approximately 3 months ago.

|  | **Yes** | **No** | **If yes, please enter the total number of times you were treated by an ambulance crew since you last completed the ABC questionnaires approximately 3 months ago** |
| --- | --- | --- | --- |
| **Treatment by an ambulance crew (whether or not you were taken to hospital by the ambulance)** |  |  |  |

1. **COMMUNITY HEALTH AND SOCIAL CARE SERVICES**

We would like to know if you have had any contacts with any health or social care professionals or services that took place in the community since you last completed the ABC questionnaires approximately 3 months ago.

For each professional or service listed, please tell us if you have had any contacts by selecting ‘No’ or ‘Yes’.

If the answer is ‘Yes’, please tell us how many contacts in total you have had with each professional or service since you last completed the ABC questionnaires approximately 3 months ago.

**Please include all contacts, whether they took place in person, by telephone or online by video conference.**

|  | **Yes** | **No** | **If yes, please enter the total number of contacts you had since you last completed the ABC questionnaires approximately 3 months ago** |
| --- | --- | --- | --- |
| **General practitioner (GP)** |  |  |  |
| **Practice nurse (a nurse based in a GP surgery)** |  |  |  |
| **Cancer nurse/breast cancer nurse in the community (please exclude any contacts with a breast cancer nurse in hospital)** |  |  |  |
| **Any other nurse in the community, for example a district nurse, health visitor or midwife** |  |  |  |
| **Cancer support specialist/cancer support worker** |  |  |  |
| **Social worker, family support worker, or any other social services worker** |  |  |  |
| **Any therapist providing ‘talking therapy’, for example cognitive behaviour therapy, counselling, mindfulness-based therapy, dialectical behaviour therapy, etc.**  ****If you are in the ABC therapy group, please EXCLUDE your use of this therapy**** |  |  |  |
| **Excluding any contacts with therapists already reported in the previous question, any other mental health worker in the community, for example a psychiatrist, a Community Psychiatric Nurse (CPN), a Community Mental Health Team (CMHT) worker, etc.** |  |  |  |
| **Excluding any contacts already reported in previous questions, any other advice or support relating to cancer (either online, over the phone or in person) from a charitable organisation such as Macmillan Cancer Support, Maggie’s Centres, Penny Brohn, Breast Cancer Now, Keeping Abreast, Flat Friends, Look Good Feel Better, OUTpatients (formerly known as Live Through This), Switchboard Black Women Rising, etc.** |  |  |  |
| **Excluding any contacts already reported in previous questions, any other advice or support relating to mental health (either online, over the phone or in person) from a charitable organisation such as the Samaritans, MIND, Macmillan, etc.** |  |  |  |

1. **MEDICATION**

We would like to know if you have been prescribed any medication by a doctor or other health professional for mental health reasons since you last completed the ABC questionnaire approximately 3 months ago. This might include, for example, medication for depression, anxiety, sleep disorders, etc.

For each medication category listed below, please tell us if you have been prescribed medication for this reason since you last completed the ABC study approximately 3 months ago by selecting ‘Yes’ or ‘No’.

Please ignore any over-the-counter medications (medications you can buy directly from a chemist/pharmacy that do not require a prescription).

| **Medication for:** | **For example:** | **Yes** | **No** |
| --- | --- | --- | --- |
| **Depression or**  **Anxiety** | Fluoxetine, Prozac, Sertraline, Lustral, Escitalopram, Cipralex, Citalopram, Cimpramil, Fluvoxamine, Faverin, Mirtazapine, Zispin, Venlafaxine, Efexor, Atomoxetine |  |  |
| **Sleep disorders** | Dexamphetamine, Dexedrine, Melatonin, Diazepine, Valium |  |  |
| **Attention Deficit Hyperactivity Disorder (ADHD)** | Methylphenidate, Ritalin, Equasym XL, Concerta XL, Medikinet XL, Dexamphetamine, Dexedrine, Intuniv, Lisdexamfetamine, Elvanse, Atomoxetine, Strattera, Guanfacine XR, |  |  |
| **Hormone blocking therapy** | Tamoxifen, letrozole, exemestane, anastrozole, goserelin, zoladex, leuproreline, lucrin |  |  |

AD-SUS designed by [name] at King’s College London. For further information please contact: King’s Health Economics, Institute of Psychiatry, Psychology & Neuroscience, King’s College London, [name]. Email: [[contact]](mailto:[contact])

